## TRIAL SUMMARY

|                                    |                                                                                                                                                                                                                                                                                                                                                    |                                                                                                                                                                                                                                                                                                                                                                                                                                        |
|------------------------------------|----------------------------------------------------------------------------------------------------------------------------------------------------------------------------------------------------------------------------------------------------------------------------------------------------------------------------------------------------|----------------------------------------------------------------------------------------------------------------------------------------------------------------------------------------------------------------------------------------------------------------------------------------------------------------------------------------------------------------------------------------------------------------------------------------|
| Trial Title:                       | AlcoChange: An Open Label Pilot Study of Smartphone Monitoring for Alcoholic Liver Disease                                                                                                                                                                                                                                                         |                                                                                                                                                                                                                                                                                                                                                                                                                                        |
| Internal ref. no. (or short title) | AlcoChange                                                                                                                                                                                                                                                                                                                                         |                                                                                                                                                                                                                                                                                                                                                                                                                                        |
| Trial Design                       | Open label, pilot                                                                                                                                                                                                                                                                                                                                  |                                                                                                                                                                                                                                                                                                                                                                                                                                        |
| Trial Participants                 | Inpatients and outpatients with alcoholic liver disease (ALD)                                                                                                                                                                                                                                                                                      |                                                                                                                                                                                                                                                                                                                                                                                                                                        |
| Planned Sample Size                | 60                                                                                                                                                                                                                                                                                                                                                 |                                                                                                                                                                                                                                                                                                                                                                                                                                        |
| Treatment duration                 | 3 months                                                                                                                                                                                                                                                                                                                                           |                                                                                                                                                                                                                                                                                                                                                                                                                                        |
| Follow up duration                 | Until end of treatment                                                                                                                                                                                                                                                                                                                             |                                                                                                                                                                                                                                                                                                                                                                                                                                        |
| Planned Trial Period               | 1 year                                                                                                                                                                                                                                                                                                                                             |                                                                                                                                                                                                                                                                                                                                                                                                                                        |
|                                    | Objectives                                                                                                                                                                                                                                                                                                                                  | Outcome Measures                                                                                                                                                                                                                                                                                                                                                                                                                |
| Primary                            | Self-reported alcohol intake                                                                                                                                                                                                                                                                                                                       | Alcohol intake by the timeline follow-back method                                                                                                                                                                                                                                                                                                                                                                                      |
| Secondary                          | 
 
- Compliance with the device.
 
- Attendance at community alcohol services following discharge.
 
- Change in health related quality of life (HRQoL)
 
- Changes in patient empowerment
 
- Factors determining compliance with app and effect on drinking behaviour
 
 | 
 
- No of interactions with the device over the study period.
 
- Follow-up rates at community alcohol services appointments over the study period.
 
- HRQoL will be assessed by SF-36 questionnaire before and after the study period.
 
- Patient empowerment will be assessed by the SUSTAINS questionnaire.
 
- Qualitative assessment at focus group
 
 |
| Tertiary / exploratory             | 
 
- Presence or absence of periodontitis in patients with ALD
 
- Change in microbial population in saliva and stool over study period
 
- Frequency of hospital admissions up to 1 year due to
 
                                                                                      | 
 
- Dental examination at baseline
 
- Sampling of saliva and stool at baseline and at 3 months
 
- Hospital Episode Statistics (HES) data to determine subsequent hospital admissions up to 1 year.
 
                                                                                                                                                                     |

[figure not shown]

|  |                        |  |
|--|------------------------|--|
|  | a complication of ALD. |  |
|--|------------------------|--|

[figure not shown]

|                     |                                                                                                                                                                                                                                                |
|---------------------|------------------------------------------------------------------------------------------------------------------------------------------------------------------------------------------------------------------------------------------------|
| Study Intervention: | AlcoChange is a smartphone application and battery-less smartphone breathalyser. AlcoChange (hereafter referred to as the device ) is CE marked as a class I in vitro diagnostic medical device under Directive 98/79/EC (IVDD). |
|---------------------|------------------------------------------------------------------------------------------------------------------------------------------------------------------------------------------------------------------------------------------------|

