### 3.3 Exploratory endpoints/outcomes

There is increasing interest in the role of oral and gut microbes in the natural history of liver disease. Additionally, periodontal disease has been associated with adverse health outcomes in diabetes mellitus and coronary heart disease, through effects of endothelial function. Importantly, endothelial dysfunction is a key component of the development of complications of cirrhosis.

The hypothesis of this part of the study is that the presence of periodontitis, or the baseline oral and gut bacterial populations, will be associated with outcomes from liver disease with one year. No individual patient data will be acquired beyond the 3-month study period, but re-admission will be obtained from Hospital Episode Statistics. Additionally, the effect of reduced alcohol intake from baseline on oral and gut microbes will be assessed, by repeat saliva and stool sampling at 3-months.

The presence of periodontitis will be assessed by dental examination, which will be conducted during the patient's inpatient stay. This will include a basic periodontal examination which should not exceed 15 min in duration. Using a manual University of North Carolina (UNC-15) periodontal probe, the tip of the probe is gently inserted into the gingival pocket and the depth of insertion measured in millimetres on the probe. Probing force should not exceed 20-25 gm. Further details of the dental examination are attached.

| Objectives        | Outcome Measures                  | Timepoint(s) of evaluation of this outcome measure (if applicable) |
|-------------------|-----------------------------------|--------------------------------------------------------------------|
| Primary Objective | Self-reported alcohol intake will | Self-reported alcohol intake will                                  |

[figure not shown]

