| 
Tertiary Objectives
 
 
- To determine the prevalence of periodontitis amongst patients with ALD.
 
- To determine changes oral and gut microbial populations over the study period.
 
- To determine if the presence of periodontitis or saliva/stool microbial populations are related to frequency of hospital admissions up to 1 year.
 
                                                                            | 
 
- The presence of periodontitis will be determined by dental examination at baseline.
 
- Microbial populations in saliva and stool will be determined at baseline and at the end of the study period.
 
- The presence of periodontitis and microbial populations in saliva and stool will be correlated with frequency and type of readmission with liver disease up to 1 year.
 
                                                                                                             | 
 
- Dental examination will be conducted at baseline, as an inpatient.
 
- Saliva and stool sampling will be conducted at baseline, as an inpatient, and again at the end of study visit at 3 months (10-14 weeks).
 
- Data on readmissions at 1 year will be obtained from Hospital Episode Statistics.
 
                                                                                                                                                                                 |

[figure not shown]

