## **6.4 Trial assessments**

The specific trial procedures are:

[figure not shown]

- Blood tests at baseline and at 3 months (as part of SOC)
- Saliva and stool collection at baseline (as an inpatient or outpatient) and at 3 months. The exact timing of sample provision will be determined by the patient – can be anytime during the patient's initial inpatient stay/**outpatient visit**, or up to 6 weeks following discharge. The patient will be provided with collection pots to provide samples at any point around 3 months (10-14 weeks).
- Dental examination at baseline.
- The only study assessments will be at baseline (either as an inpatient or an outpatient) and at the 3-month (10-14 week) outpatient clinic visit, which is part of SOC. No dedicated study visits will be required.
- The patient will be supplied with the device and training provided. If the patient is having difficulty with the device, contact will be provided telephone or in person to provide further training as required.

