### 6.5 Long term follow-up assessments

There will be follow-up of participants beyond the 3-month study period. Data on hospital admissions up to 1 year will be assessed by accessing Hospital Episode Statistics data.

Patients that do not attend a follow-up clinic visit between 10-14 weeks will be contacted by telephone during the period 14-16 weeks following recruitment, to make arrangements to conduct the interview regarding alcohol consumption over the preceding 3 months (either in person or by telephone). If the patient cannot be contacted by week 16, then no further attempts to contact the patient by telephone will be made.

In case of premature discontinuation, similarly the research team will attempt to contact the patient by telephone within 14 days after discontinuation, to conduct the alcohol consumption interview. In this case, statistical analysis will be conducted by the Last Observation Carried Forward method.

Patients who complete the above assessments may be contacted up to 52 weeks following inclusion, to ask willingness to participate in a focus group (up to 12 participants, as described in 3.2 above).

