### 8.5 Recording and reporting of Adverse/Serious Adverse Events (non device related events)

The Investigator or appropriate site personnel will examine any subject experiencing an AE as soon as possible. The Investigator will do whatever is medically necessary for the safety and well-being of the subject. The subject will remain under observation at the Investigator's discretion. All AE's observed or reported following use of the AlcoChange device will be followed by the Investigator until resolved or until medically stabilized.

Whenever possible, the AE will be described on the appropriate CRF using standard medical terminology in order to avoid the use of vague, ambiguous, or colloquial expressions.

During the study, the Investigator or study site personnel will be responsible for querying and recording all adverse events (AEs) and serious adverse events (SAEs). Adverse events will be recorded from the date of signature of the informed consent until completion of the study at month 3 and will be evaluated by the Investigator for severity, seriousness, and relationship to study intervention, as outlined below. Untoward medical events which occur *after* signature of the informed consent *but before* use of the breathalyzer will be recorded as medical history. SAEs will be recorded from the signature of the consent form until 30 days after the last use of the breathalyzer.

Subjects will be asked at intervals throughout their assessments and again at the 3-month follow-up appointment about the occurrence of any adverse events. All AEs will be graded according to the criteria below. Additionally, the Investigator will determine the AE's relationship to the investigational device as described below. Adverse events will be followed by the Investigator until they have returned to baseline or stabilize.

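### SAEs are to be recorded until 30 days after last breathalyser use, but no collection step is planned after the 10-14 week visit, and the follow-up statements conflict with one another

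*Combined protocol and SAP*

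**What the plan says.** Several places state when follow-up ends, and they differ.

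- Trial Summary, follow-up duration row: "Until end of treatment", with treatment lasting 3 months.
- Trial Summary, exploratory outcomes: "Hospital Episode Statistics (HES) data to determine subsequent hospital admissions up to 1 year".
- Section 3.3, text: "No individual patient data will be acquired beyond the 3-month study period, but re-admission will be obtained from Hospital Episode Statistics".
- Section 3.3, objectives table: periodontitis and the microbial findings "will be correlated with frequency and type of readmission with liver disease up to 1 year".
- Section 6.4: "The only study assessments will be at baseline (either as an inpatient or an outpatient) and at the 3-month (10-14 week) outpatient clinic visit".
- Section 6.5: "There will be follow-up of participants beyond the 3-month study period". The source named is HES to 1 year, and participants may be approached for a focus group up to week 52.
- Section 8.5: AEs are recorded to month 3, but "SAEs will be recorded from the signature of the consent form until 30 days after the last use of the breathalyzer". Patients are asked about events during their assessments and at the 3-month appointment.
- Table 1 (section 6): adverse events are marked at baseline and at 3 months. In the 14-52 week column only the focus group is marked.

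**The concern.** The SAE window is defined by device use, and the opportunities to ask about SAEs are defined by visits. For anyone still using the breathalyser near the 3-month visit, the window outlasts the last planned question about adverse events. The protocol sets a duty to record but names no step by which events in the remaining days would be found.

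This affects patients who attend as planned, and it is greatest for those who use the device to the end. In-patient hospitalisation is serious by the definition in section 8.1, so a hospital admission shortly after the visit is a typical event that could be missed. At stake is whether a reported SAE count would cover the period that the protocol states.

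Separately, the summary row and the opening clause of the section 3.3 sentence do not fit the 1-year readmission work, which needs each patient's admissions tied to that patient's baseline findings.

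**Working it through.** The plan gives no figure of its own to reproduce: section 9 has no formal sample size calculation, and no SAE rate is stated. The check compares time windows.

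**Inputs**

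- Visit at week 10-14, that is day 70 to day 98 (sections 3.1 and 6.4, Table 1).
- End of SAE window = day of last breathalyser use + 30 (section 8.5).
- No adverse-event check after the visit (Table 1, sections 6.4 and 8.5).
- Readmitted completers: Table S2 shows 13 + 5 + 12 = 30 with none, so 41 - 30 = 11; Table S4 gives 10 of 41.

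**1. Length of the gap.** Uncovered days = max(0, day of last use + 30 - day of visit). If last use is on the day of the visit:

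| Visit | Window ends | Uncovered | Share of window |
|---|---|---|---|
| Day 70 | 70 + 30 = day 100 | 30 days | 30/100 = 30% |
| Day 98 | 98 + 30 = day 128 | 30 days | 30/128 = 23% |

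**2. Who is unaffected.** The gap is zero if last use was at least 30 days before an attended visit: by day 70 - 30 = 40 for a week-10 visit, or by day 98 - 30 = 68 for a week-14 visit. Between these cases the gap is partial; last use 15 days before the visit leaves 15 days uncovered.

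**3. Whether other contacts close it.** Section 6.5 plans telephone calls in weeks 14-16 (days 98-112), but only for patients who missed the visit, and their stated purpose is the alcohol interview. After premature discontinuation a call is attempted within 14 days, for the same purpose. If last use coincides with discontinuation, at least 30 - 14 = 16 days of the window remain after that call.

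**4. Illustrative size.** Assume that first readmissions are spread evenly over the 9 months from month 3 to month 12 (3 x 91 = 273 days), and that every readmitted patient used the device up to the visit:

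- Table S2: 11 x 30/273 = 1.2 patients
- Table S4: 10 x 30/273 = 1.1 patients

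If only the two readmitted patients with more than 60 logins (14 - 12 = 2) had used it to the visit, the figure would be 2 x 30/273 = 0.2. Logins are only a proxy for the date of last breathalyser use.

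**5. Readmission statements side by side.** Taken alone, the first clause of the section 3.3 sentence rules out individual data after 3 months, but its second clause names HES as the source for readmission. Section 6.5 states follow-up beyond 3 months from the same source. Section 10.1 has the chief investigator keep enough information to link CRFs, hospital records and samples. Tables S2 and S4 break readmissions down by login group, which requires patient-level data. The route therefore exists. What conflicts with it is the summary row and the first clause of section 3.3, and HES is missing from the source-data list in section 10.1. The focus groups, allowed up to week 52, do not fit that first clause either.

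**The case against.** The strongest reply is that no planned contact does not mean no recording. Section 8.5 makes SAE recording to 30 days after last use a duty, and the protocol sets out a reporting route to the sponsor. Nothing confines ascertainment to visits. The study is single-centre, and the alcohol liaison team is part of the normal clinical team, so local admissions may come to notice. The device is a CE-marked breathalyser and app in a single-arm pilot described as low risk, and the primary analysis is untouched. All of this stands, and it limits the weight of the point. It does not supply the missing step: nobody is assigned to look for events after the visit, and admissions elsewhere would depend on chance report.

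A reader might infer that neither the SAE window nor the 1-year readmission objective can be delivered as written. The documents do not support that. For readmission, the HES clause in section 3.3, section 6.5 and the summary's own outcome row give a data source, and the supplement shows that such data were obtained. For SAEs, spontaneous reports and hospital records remain open.

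A reader might also infer that the trial's SAE count did fall short. The documents contain no SAE results, so this cannot be checked.

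**Conclusion.** The point holds as a gap in planned SAE collection together with a conflict of wording. For a patient who uses the breathalyser up to the 3-month visit, 30 of 100-128 days (23-30%) of the SAE window have no planned collection. The gap shrinks as last use moves earlier, and it vanishes when last use is at least 30 days before an attended visit. This assumes that use ends at the visit; later use would move the end of the window later still.

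The number of events lost is unknown. About 1 completer with an admission in the uncovered month is an upper illustrative figure under even spread and use to the visit by all. It is not a strict bound: the readmission period is not stated, Tables S2 and S4 disagree by one patient, Table S2 counts alcohol-related readmissions only, and both tables leave out the 24 of 65 patients whom Table S1 lists as not completing.

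The 1-year readmission objective is deliverable, so only the wording needs reconciling there. The change is worth making because it is cheap and would alter which SAE data are captured. The primary outcome is not affected.

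**What to change.** Reconcile the Trial Summary follow-up row, section 3.3 (text and objectives table), Table 1, and sections 6.4, 6.5 and 8.5:

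- State three end points: the 3-month visit for the alcohol interview and AEs; 30 days after last breathalyser use for SAEs, as section 8.5 already has it; and 1 year for patient-linked HES.
- Reword the section 3.3 sentence rather than delete it, since it carries the HES provision. It should say that the only individual data acquired after 3 months are SAEs to 30 days after last use, linked HES admissions and focus-group data, plus the catch-up interview that section 6.5 allows to week 16.
- Add HES to the source data in section 10.1.
- Check the planned HES extract for admissions in each patient's 30-day post-use window, take the date of last breathalyser use from the platform log, and add any admission found to the SAE listing.

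The cost is protocol wording and one more query on an extract already planned; no new visit is needed. There are three downsides. HES data arrive late, so they help complete the count but do not support expedited reporting. HES captures admissions only, so serious events without an admission still depend on being reported. Consent must also cover patient-level HES linkage; the consent pages are not among the documents reviewed, so whether they already do is not known.
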